## 9.2 Procedures for Recording and Reporting Adverse Events

The Medicines for Human Use (Clinical Trials) Regulations 2004 and Amended Regulations 2006 gives the following definitions:

**Adverse Event (AE):** Any untoward medical occurrence in a subject to whom a medicinal product has been administered including occurrences which are not necessarily caused by or related to that product.

**Adverse Reaction (AR):** Any untoward and unintended response in a subject to an investigational medicinal product which is related to any dose administered to that subject.

**Unexpected Adverse Reaction (UAR):** An adverse reaction the nature and severity of which is not consistent with the information about the medicinal product in question set out in the summary of product characteristics (SmPC) for that product (for products with a marketing authorisation)

**Serious adverse Event (SAE), Serious Adverse Reaction (SAR) or Unexpected Serious Adverse Reaction (USAR):** Any adverse event, adverse reaction or unexpected adverse reaction, respectively, that:

- Results in death;
- Is life-threatening;
- Required hospitalisation or prolongation of existing hospitalisation
- Results in persistent or significant disability or incapacity;

- Consists of a congenital anomaly or birth defect.

**Suspected Unexpected Serious Adverse Reaction (SUSAR)** – A Suspected Unexpected Serious Adverse Reaction is a serious adverse drug reaction, the nature and severity of which is not consistent with the information about the medicinal product in question set out:

- In the case of a product with a marketing authorisation, in the summary of product characteristics for that product.
- In the case of any other investigational medicinal product, in the investigator's brochure relating to the trial in question.

### **Important Medical Events (IME) & Pregnancy**

Events that may not be immediately life-threatening or result in death or hospitalisation but may jeopardise the patient or may require intervention to prevent one of the other outcomes listed in the definition above should also be considered serious.

Although not a serious adverse event, any unplanned pregnancy will also be reported via the SAE reporting system.

### **Reporting Responsibilities**

*King's College London and South London and Maudsley NHS Foundation Trust* have delegated the delivery of the Sponsor's responsibility for Pharmacovigilance [as defined in Regulation 5 of the Medicines for Human Use (Clinical Trials) Regulations 2004] to the King's Health Partners Clinical Trials Office (KHP-CTO).

All SAEs, SARs and SUSARs will be reported immediately by the Chief Investigator (and certainly no later than 24hrs) to the KHP-CTO in accordance with the current Pharmacovigilance Policy. The KHP-CTO will report SUSARs to the regulatory authorities (MHRA, competent authorities of other EEA (European Economic Area) states) in which the trial is taking place.

The Chief Investigator will report to the relevant ethics committee. Reporting timelines are as follows:

SUSARs which are fatal or life-threatening must be reported not later than 7 days after the sponsor is first aware of the reaction. Any additional relevant information must be reported within a further 8 days.

SUSARs that are not fatal or life-threatening must be reported within 15 days of the sponsor first becoming aware of the reaction.

The Chief Investigator and KHP-CTO (on behalf of the co-sponsors), will submit a Development Safety Update Report (DSUR) relating to this trial IMP, to the MHRA and REC annually.

### **9.2.1 Adverse events that do not require reporting**

All SAEs will be reported for this trial except hospitalisations due to deterioration in mental state, as we anticipate a high proportion of our participants will be hospitalised for this reason during the trial.

The period for AE reporting is from consent to 28 days post last IMP administration. All AEs will be reported.

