**At the assessment visits (Baseline and 6 months) participants will be required to complete the following assessments:**

- a) Mental health care: A list of current medications; medication history, including antipsychotic, antidepressant, mood stabilisers, non-psychiatric medications and non-prescription drugs and vitamin supplements will be gathered at each time point. We will establish the duration of untreated psychosis (DUP) at baseline using the Nottingham Onset Schedule (NOS). Use of key NHS services contact questionnaire will measure the total number of hospital admissions and the amount of contact with the home treatment team throughout the duration of the trial. This will be recorded from the time of consent up to the Month 6 assessment. Data will be collected from patients at their final assessment and checked against medical notes. For patients who are lost to follow-up, this data will be obtained from medical notes only.
- b) Biomedical / Cardiovascular status (secondary endpoint) will be measured at each time point as: waist circumference, weight, height (for BMI), blood pressure, heart rate (pulse) (Anthropometric measures), along with blood measures of cardiovascular risk / inflammatory markers and smoking habits. (Measures which form part of routine clinical care will be shared with the clinical team if the patient wishes).
- c) Mental health status (primary and secondary endpoints): the Positive and Negative Syndrome Scale (PANSS); Global Assessment of Functioning (GAF). The GAF will be rated first, from clinical notes at the time of first presentation to services for psychosis and then again at baseline to ensure an accurate representation of functioning at both the onset of illness and at the time of consent; Calgary Depression Scale (CDS); OPCRIT (Operational Criteria checklist) will be performed during the trial to ensure that we have a researcher-led clinical rating independent of the diagnosis retrieved from clinical notes at the time of screening.

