### **Safety of Vitamin D**

These analyses are based in the safety data and describe safety outcomes. Chi squared tests (Fisher's Exact test where expected count in any cell is less than 5) will be used to describe any differences. SAEs will be defined in accordance with the EU clinical trial directives. The potential adverse events that we have anticipated we will summarise separately.

AEs will be tabulated by event type and clinical classification by time, phase and randomised group. Each table will detail the number of participants that were still in the trial at the time points by randomisation group. If any adverse events are selected as being of interest they will be further summarised; outlining the severity (mild, moderate, severe) and if classified serious, the expectedness (expected, unexpected) of the event. Any death will be reported as a serious adverse event.

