### Missing outcome data

The mixed model will be fitted using maximum likelihood methods that are valid under the MAR assumption. However, this assumption relates to the variables that are included in the model. To allow for a variable which predicts missingness, this variable needs to be included as either one of the explanatory or dependent variables in the model. Should the investigation into missingness indicate any demographic or clinical baseline variables that are predictors of outcome missingness then such variables will be included as covariates in the model if deemed suitable for adjustment.

If post treatment variables such as compliance with treatment, or baseline variables not suitable to adjust for in the main analyses, are found to be predictive of drop out, multiple imputation will be considered.

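### The by-arm SAE comparison is likely to leave out mental-state admissions that its stated definition includes, and the admissions collected to Month 6 have no planned by-arm summary.

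*Combined protocol and SAP*

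**What the plan says.** **Reporting.** Protocol 9.2 lists among its seriousness criteria "Required hospitalisation or prolongation of existing hospitalisation", with no restriction on cause. Its Reporting Responsibilities paragraph says "All SAEs, SARs and SUSARs will be reported immediately by the Chief Investigator". Section 9.2.1 then makes an exception: "All SAEs will be reported for this trial except hospitalisations due to deterioration in mental state". The reason given is that such events should be frequent: "as we anticipate a high proportion of our participants will be hospitalised for this reason during the trial". The same section also says "All AEs will be reported".

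**Analysis.** SAP 1.9 promises SAE prevalence by arm. SAP 2.6 promises AEs, ARs, SAEs and SARs by arm and time point. The safety part of SAP 3.1.2 compares arms with chi-squared or Fisher tests and says "SAEs will be defined in accordance with the EU clinical trial directives". None of these places mentions the exemption.

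**Data collected.** Protocol 7.1(a) records the number of hospital admissions and the amount of home-treatment-team contact, from consent to the Month 6 assessment, by patient report checked against notes. It adds "For patients who are lost to follow-up, this data will be obtained from medical notes only". In the SAP these data appear only as the Service Contacts Form row of the assessment schedule (baseline and 6 months). They are not an endpoint (Protocol 4.2), a secondary outcome (SAP 3.1.2) or a named safety summary (SAP 2.6 and 3.1.2).

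**Missing data.** SAP 3.1.3 says that if post-treatment variables, or baseline variables unsuitable for adjustment, "are found to be predictive of drop out, multiple imputation will be considered". SAP 1.9 and 3.1.4 plan sensitivity analyses for departures from MAR.

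**The concern.** A statistician following the SAP would build the SAE table from the SAEs in the trial database, and the exempt admissions would probably not be among them. The table would carry a definition that covers every hospitalisation while leaving out the kind of hospitalisation the protocol expects to be frequent. A reader could not tell this from the table.

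In a psychosis trial, admission for worsening mental state is an event on which an imbalance between arms would matter, whether it pointed to harm or to benefit. The data to show such an imbalance are being collected, including for people whose 6-month PANSS is missing because they were lost to follow-up. As written, an imbalance in either direction has no planned place in the report.

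**Working it through.** **1. The passages side by side.**

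| Place | Is a mental-state admission counted? |
|---|---|
| Protocol 9.2, SAE definition | Yes: any hospitalisation |
| Protocol 9.2, Reporting Responsibilities | Yes: all SAEs, no exception stated |
| Protocol 9.2.1, first sentence | No: exempt from SAE reporting |
| Protocol 9.2.1, last sentence | Yes, as an AE: all AEs reported |
| SAP 3.1.2, safety | Yes: directive definition, no exemption |
| SAP 2.6 | Not stated |

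These can be read together only by choosing among them. The event could end up in the SAE table, in the AE tables only, or in neither.

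**2. The plan's own figures.** 240 × (1 − 0.20) = 192, or 96 per arm, as stated. With SD 15 and two-sided 5%, the detectable difference at 80% power is 15 × (1.96 + 0.842) × √(2/n per arm). This gives 5.94 at N = 200 and 6.26 at N = 180 (5.97 and 6.30 with the t distribution), against 6 and 6.3 stated. The plan's figures are reproduced. The 20% attrition leaves 240 − 192 = 48 participants without a 6-month PANSS.

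**3. How many participants the exemption could touch.** No rate is given, so these are assumptions. At 10%, 20%, 30% and 40% admitted in both arms, 240 × rate = 24, 48, 72 and 96 participants. If the arms differed, say 20% against 30%, then 120 × 0.20 = 24 and 120 × 0.30 = 36 participants would be missing from an SAE table built on reported SAEs.

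**4. What a by-arm table could show.** The standard error of a difference in proportions at 120 per arm is √(2p(1 − p)/120). It is 0.039, 0.052, 0.059 and 0.063 at the four rates, so the 95% interval is about ±8 to ±12 points. At 80% power the detectable reductions are about 8.5, 12.5, 15.1 and 16.8 points. The table is descriptive, but it would show a large imbalance.

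**5. Effect on the primary estimate (assumptions throughout).** Let admission raise 6-month PANSS by D, let p be the admission rate in an arm, and let m1 and m0 be the missing proportions in admitted and non-admitted participants. With no other arm effect, the true difference is D × (p_placebo − p_active). The excess in an arm's observed mean is D·p(1 − m1) / [p(1 − m1) + (1 − p)(1 − m0)].

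- Mild case: D = 10, p = 0.20 v 0.30, m1 = 0.40, m0 = 0.135. Observed: 10 × 0.18/0.7855 − 10 × 0.12/0.812 = 2.29 − 1.48 = 0.81. True: 1.00. Shift: 0.19.
- Extreme case: D = 15, p = 0.10 v 0.30, m1 = 0.60, m0 = 0.10. Observed: 15 × 0.12/0.75 − 15 × 0.04/0.85 = 2.40 − 0.71 = 1.69. True: 3.00. Shift: 1.31.
- Equal admission rates: no shift.

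Both unequal cases give about 20% missing overall. Simulations that also condition on baseline and 3-month PANSS, over similar ranges, give shifts of about 0.1 to 1.3 units. The shift is smaller when the admission already shows in the 3-month score. Adding an admission indicator removes it.

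**The case against.** **On the SAE table.** Section 9.2.1 can be read as an explicit exception to a general expedited-reporting rule, which is not a contradiction. It also says all AEs are reported, and AEs are tabulated by arm, so a deterioration could still appear there. SAP 3.1.2 promises a separate summary of anticipated adverse events, which might be meant to cover these admissions. This stands in part: it is not settled that the admissions vanish from every table. But the SAP does not list the anticipated events or mention the exemption, and an AE entry would not correct an SAE table whose definition includes the event.

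**On the missing-data model.** A reader might infer that the primary analysis ignores admissions and is seriously biased. The documents do not support that. SAP 3.1.3 adds suitable baseline predictors of missingness and allows multiple imputation for post-treatment ones, with compliance only as an example. Analyses under departures from MAR are planned. Protocol 5.6 asks for 6-month data even outside the window, and recruitment includes inpatient units, so admission need not mean a missing PANSS. The larger shifts need a marked arm imbalance, a rise of a full SD and a wide missingness gap together. What remains is that admission is not named and imputation is only to be considered.

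**On the data.** Protocol 7.1(a) does not say that the reason for admission is recorded, and it does not address participants who withdraw consent. A complete record of psychiatric admissions in every participant should not be assumed. Calling admission the most informative event would be a judgement with no figure behind it.

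**Conclusion.** The point holds for the safety comparison. As written, the by-arm SAE table is likely to leave out a class of serious events that the protocol itself expects to be common, and so not match its stated definition. The admissions and home-treatment contacts collected to Month 6 have no planned by-arm summary. The number affected cannot be taken from the documents. At assumed rates of 10% to 40% it is 24 to 96 of 240.

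The consequence for the primary analysis is secondary and conditional. Under the assumed ranges the shift is about 0.1 to 1.3 PANSS units towards zero, and nil if admissions do not differ by arm. That compares with 6 to 6.3 units powered for and an unadjusted standard error of 15 × √(2/96) = 2.2. This supports optional extra prespecification. It does not show that the primary model is wrong.

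**What to change.** - Reconcile the Protocol 9.2 definition, the Reporting Responsibilities paragraph, Protocol 9.2.1 and SAP 3.1.2, so that it is clear whether an exempt admission is recorded as an SAE, as an AE only, or only on the Service Contacts Form. The expedited-reporting exemption itself need not change for this.
- Label the by-arm SAE table as excluding the exempt admissions, and point to the table that shows them.
- In SAP 2.6 and 3.1.2, add a by-arm table from the Service Contacts Form, for the final report and the DMC: participants with at least one post-randomisation hospital admission, and total admissions. Show all causes, with psychiatric admissions separately where the reason is recorded. Distinguish admissions already ongoing at randomisation, because inpatients are recruited and the form counts from consent. State how many participants have no admission data.
- Optionally, in SAP 3.1.3 and 3.1.4, name post-randomisation admission as a candidate auxiliary variable in a multiple-imputation sensitivity analysis of 6-month PANSS. It should not be a covariate in the primary model, because it occurs after randomisation and may be affected by treatment.

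The cost is SAP wording and one extra table from a form already in use, plus one imputation analysis if the option is taken. If the reason for admission is not recorded, the psychiatric breakdown cannot be produced and the all-cause table stands alone.

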### 9.3 Treatment Stopping Rules

The trial may be prematurely discontinued by the Sponsor, Chief Investigator or Regulatory Authority on the basis of new safety information or for other reasons given by the Data Monitoring Committee, Trial Steering Committee, regulatory authority or ethics committee concerned.

If the trial is prematurely discontinued, active participants will be informed and no further participant data will be collected. The Competent Authority and Research Ethics Committee will be informed within 15 days of the early termination of the trial.

## 10. Statistics

### 10.1 Sample Size

A total of 240 first episode psychosis patients will be recruited over a 2 year period.

#### Power Calculation

Based on recently collected PANSS Total score in FEP patients collected as part of the Physical Health and Substance Use Measures in first episode Psychosis (PUMP) study ( $n = 190$ ), the mean (and standard deviation) score was 58.1 (15.0) units. Based on the number of new cases presenting to FEP services, and based on the annual counts of FEP patients recruited into similar studies, we predict that we will recruit and randomise 120 patients per year (i.e. 240 over two years).

The primary intention to treat (ITT) analyses will compare two equally sized treatment arms, treatment or placebo on the PANSS scale at 6 months post-randomisation. For the power analyses, we modelled two plausible scenarios. For the primary outcome (6 month follow-up), we assumed a 20% attrition proportion. After 20% attrition the effective sample size is 192 (96 in each trial arm).

Based on  $\alpha = 0.05$  and power = 80%, samples between 200 and 180 participants will be able to confidently detect mean PANSS total score group differences of between 6 and 6.3 units. This equates to a standardised effect of size of approximately 0.4 to 0.42.

Considering 90% power with the same power assumptions, we will be able to detect mean PANSS total score group differences of between 6.9 and 7.3 units (standard effect size from 0.46 to 0.49). Thus, we should be able to detect moderate effect sizes if present.

As a secondary objective, we also wish to estimate the average treatment effect in those participants who meet the vitamin D deficiency threshold. We assume 60% of the FEP

population have vitamin D concentrations below 50 nmol/L. At 6 months after 20% attrition (sample now = 192) and 60% who meet the vitamin D threshold, this will result in a projected sample size of 115.

Based on  $\alpha = 0.05$  and power = 80%, samples between 120 and 100 participants will be able to confidently detect mean PANSS total score group differences of between 7.7 and 8.5 units. This equates to a standard effect of size of 0.52-0.57. Considering 90% power with the same power assumptions, we will be able to detect mean PANSS total score group differences of between 9.8 and 8.95 units (standardised effect size from 0.60 to 0.65).

## 10.2 Analysis

The primary analyses of efficacy will be based on the intention-to-treat sample, utilising all available follow-up data from all randomised participants. The significance level will be 5% (2-sided) for all specified main and secondary analyses with estimates and confidence intervals presented for all effects.

All descriptive analyses, recruitment rate, consent rate, loss to follow-up, departures from randomised treatment and the prevalence of serious adverse events post-randomisation will be reported and summarised by treatment arm over the course of the study. All causes of withdrawal from randomised treatment will be reported. BMI will be calculated using the following formula:  $\text{weight (kg)}/\text{height (m)}^2$ .

The main objective of the formal statistical analyses is to assess the effect of vitamin D supplementation on the primary outcome PANSS total Score at the 6 month follow-up time point. To this end linear mixed modelling (LMM) will be employed.

In such models the outcome variable measured at the post treatment time points (here 3 and 6 months) features as the dependent variable with, treatment arm (vitamin D or placebo), time (3 or 6 months), baseline PANSS and randomisation stratifier (ethnicity) included as covariates. The model will also contain a subject-varying random intercept to account for any correlation between the repeated measures.

Treatment effects on secondary outcomes will be assessed using similar modelling techniques, employing generalisations to non-normal data where necessary.

We will also estimate subpopulation (baseline vitamin D insufficient and sufficient) specific treatment effects for the primary outcome and secondary outcomes except for 25OHD blood concentration levels by including relevant interaction terms between baseline vitamin D insufficiency status and treatment group in the statistical models.

We expect there to be some missing data in the post-treatment outcomes variables. The LMM analyses are based on maximum likelihood and will provide valid inferences under a missing at random (MAR) missingness mechanism. We will explore predictors of missingness, if deemed suitable for adjustment we will include these as explanatory variables in the analyses. If post

randomisation variables are identified a Multiple Imputation [White, I.R., P. Royston, and A.M. Wood, *Multiple imputation using chained equations: Issues and guidance for practice*. Statistics in Medicine, 2011. **30**(4): p. 377-399] model will be considered instead.

For those participants who initially signed up to a 12-month trial, we will not perform any statistical analysis on the 12-month data, but we believe it is ethically correct to assess those patients at the 12 month follow up visit as originally planned.

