### 4.2 Trial Endpoints

#### **Primary endpoint:**

Total PANSS score at 6 month follow-up.

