##### **3.1.1 Analysis of primary outcomes**

###### **Primary Efficacy Parameters**

- A. To determine whether the addition of 120,000 IU monthly of vitamin D supplement to standard treatments is more effective than placebo in improving PANSS total score at six-month follow-up in those with First Episode Psychosis

The main objective of the statistical analyses is to assess the effect of vitamin D supplementation on the primary outcome PANSS total score at the 6-month follow-up time point. To this end linear mixed modelling (LMM) will be employed.

Linear mixed modelling utilises all available information, leading to more precise estimates of the treatment effect at the time points. This technique will allow the simultaneous modelling of the repeated outcome time points, description of the course of the outcomes over time in the two intervention groups and evaluate the resulting differences between the groups.

Prior to modelling the longitudinal effect of the intervention groups over the time course of the study, spaghetti plots will be used to examine patterns of the outcome over time.

The total scores are assumed to arise from a normal distribution. This will be checked and if this is found not to be appropriate, transformations may be used.

In such models the outcome variable measured at the post treatment time points (here 3 and 6 months) features as the dependent variable with, with treatment arm (vitamin D or placebo), time (3 or 6 months), time by treatment arm interaction, baseline PANSS and the randomization stratifier (ethnicity) included as covariates.

In this longitudinal analysis, each participant acts as a cluster. Therefore, for the random part of the model, random intercepts that vary at the participant level will be used.

The Stata command 'mixed' will be used to fit the model. Treatment differences will be estimated for each time point separately using the 'lincom' command, enabling the outcome at the primary endpoint to be found this way.

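### Protocol 10.2 lists a primary model with no treatment-by-time term, so as written it gives one effect pooled over 3 and 6 months, whereas SAP 3.1.1 specifies the 6-month contrast that the endpoint needs

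*Combined protocol and SAP*

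**What the plan says.** Protocol 4.2 defines the primary endpoint as "Total PANSS score at 6 month follow-up" and lists PANSS total at 3 months as a separate secondary endpoint. Protocol 10.2 repeats that the main aim is the effect at the 6-month time point. It then describes a linear mixed model in which the 3- and 6-month scores are the dependent variable, with "treatment arm (vitamin D or placebo), time (3 or 6 months), baseline PANSS and randomisation stratifier (ethnicity) included as covariates" and a subject-level random intercept. It gives no product of arm and time, and it does not say which coefficient or contrast is the primary result.

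SAP 3.1.1 describes the same model with one addition. Its list also contains "time by treatment arm interaction, baseline PANSS and the randomization stratifier (ethnicity) included as covariates", and it says that the treatment difference will be obtained separately at each time point with Stata's lincom command, which yields the 6-month result.

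On versions, SAP 1.10 is dated 10 April 2019 and says it was written with reference to protocol V9.2 of 1 October 2018. The protocol in hand is V10.1, dated 3 May 2019. It is later than the SAP and does not list the interaction.

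**The concern.** With arm and time as main effects only, the model assumes that the treatment effect is the same at both visits and estimates that one common value. If benefit builds over the dosing period, the coefficient understates the 6-month effect. If benefit fades, it overstates it. In neither case can the model report the 3-month and 6-month effects separately, although the protocol lists both.

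Protocol 10.2 applies similar models to the secondary outcomes, so the three PANSS subscores, each due at 3 and 6 months, inherit the omission. For the vitamin D subgroup, protocol 10.2 mentions interactions of baseline status with treatment, while SAP 3.1.1 uses a three-way term with time.

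At stake is whether the primary analysis is described in one way only. A reader holding protocol V10.1 could regard the SAP analysis as a departure from it.

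**Working it through.** **1. Inputs from the documents.** Two-sided 5% level and SD 15.0 ("the mean (and standard deviation) score was 58.1 (15.0) units"). 240 randomised 1:1 with 20% attrition gives 240 × 0.8 = 192, or 96 per arm. The sample-size section claims that 200 down to 180 analysed patients give 80% power for "mean PANSS total score group differences of between 6 and 6.3 units".

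**2. Reproducing the plan's own figure.** Detectable difference = SD × (1.960 + 0.842) × √(4/N).
- N = 200: 15 × 2.802 × 0.1414 = 5.94
- N = 180: 15 × 2.802 × 0.1491 = 6.27
- N = 192: 15 × 2.802 × 0.1443 = 6.07

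The stated 6 to 6.3 is reproduced. It rests on a two-group comparison at 6 months alone. The SAP contrast matches that comparison; a coefficient pooled over two visits does not.

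**3. What each model estimates.** Write d3 and d6 for the true effects at 3 and 6 months, and ρ for the within-person correlation of the two scores.
- SAP contrast: estimates d6, whatever d3 is. With complete data, SE = SD × √(4/N) = 15 × √(4/192) = 2.165.
- Protocol model: estimates (1 − w) × d3 + w × d6. If n3 and n6 participants per arm are seen at 3 and 6 months, and everyone seen at 6 was also seen at 3, generalised least squares gives w = n6 / [2 × n6 + (1 + ρ)(n3 − n6)].

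With complete data w = 0.5, and SE = 2.165 × √((1 + ρ)/2). For ρ = 0.4 this is 1.811; for ρ = 0.6 it is 1.936.

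**4. Assumptions not in the documents.** ρ from 0.4 to 0.6, the 3-month effects below, SD 15 at both visits, and no variance reduction from baseline PANSS. Power = Φ(effect/SE − 1.960).

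| Assumed effect at 3, 6 months | Protocol model estimate | Protocol model: chance of rejecting | SAP 6-month contrast: chance of rejecting |
|---|---|---|---|
| 3, 6.1 (builds) | (3 + 6.1)/2 = 4.55 | 71% (ρ = 0.4) to 65% (ρ = 0.6) | 80% |
| 6.1, 6.1 (constant) | 6.1 | 92% to 88% | 80% |
| 5, 0 (fades) | 2.5 | 28% to 25% | 5% |

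For the first row, 4.55/1.811 = 2.512 and Φ(0.552) = 0.71; 4.55/1.936 = 2.350 and Φ(0.390) = 0.65. For the SAP contrast, 6.1/2.165 = 2.818 and Φ(0.858) = 0.80. The shortfall in the estimate is (6.1 − 4.55)/6.1 = 25%.

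**5. Incomplete data.** The weights are equal only when both visits are complete. With 120 per arm at 3 months, 96 at 6 months and ρ = 0.5, w = 96/(192 + 1.5 × 24) = 96/228 = 0.42. For ρ from 0.3 to 0.7, w runs from 0.43 to 0.41. In the building scenario the estimate becomes 3 + 3.1 × 0.43 = 4.33 down to 3 + 3.1 × 0.41 = 4.27, slightly further from 6.1.

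**The case against.** The strongest reply is that the SAP has already settled the matter. SAP 3.1.1 has the interaction and the contrast, and the SAP's amendment log records the term under version 1.9, describing it as a clarification. Protocol 10.2 and SAP 3.1.1 state the same 6-month target, so the protocol text can be read as an abbreviated summary. The SAP's purpose statement says that the primary papers are intended to follow it, and the protocol's publication policy refers to a statistical analysis strategy agreed by the Trial Steering Committee. The power losses in the table arise only if the analyst sets the SAP aside, and they depend on 3-month effects and correlations that no document gives. No passage suggests the fading pattern.

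Most of this stands, and it limits the practical risk. It does not make protocol 10.2 correct: the section lists the model's terms and the interaction is not among them.

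Two stronger readings are tempting. A reader might infer from the dates that the protocol is the governing document and that its pooled effect is therefore the official primary estimate. No passage gives the protocol precedence, nothing shows that V10.1 reconsidered and rejected the interaction, and 10.2 does not name the pooled coefficient as the result. A reader might also infer that the model could be chosen after seeing the data. The SAP had fixed the interaction in writing by version 1.9, the trial runs to December 2019, no interim analysis is planned, and the statistician stays blind until the main analyses are complete. Reverting to the protocol model would be a visible departure from the SAP.

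**Conclusion.** Protocol 10.2 is wrong as written for its own endpoint. The listed model yields one effect pooled over the two visits, which is the 6-month effect only if the effect is constant, and it cannot supply the 3-month endpoint. The SAP specifies the right model and contrast, so what remains is an unreconciled difference between two current documents with no precedence rule. Severity is moderate.

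The size is conditional. Under the building scenario (3 then 6.1 units, 192 complete, SD 15, correlation 0.4 to 0.6, no baseline adjustment), the protocol model is about 25% low, with 65–71% power against 80%. With complete data the 25% does not depend on the SD or the correlation, only on the assumed 3-month effect. The power figures depend on all the assumptions, and baseline adjustment would change them for both models. If the SAP is followed, none of this loss occurs.

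**What to change.** Before unblinding, amend the model sentence in protocol 10.2 to include the treatment-by-time interaction, and state that the primary result is the treatment contrast at 6 months, as in SAP 3.1.1. Use the same wording for the repeatedly measured secondary outcomes, with the 3-month contrast supplying the 3-month endpoints, and match the subgroup terms to the SAP's three-way interaction. Under its terms of reference in protocol section 11, the Trial Steering Committee should agree the change before it takes effect.

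The cost is a sentence or two in a protocol amendment, with no new data and no change to the sample size. Updating the SAP's reference from protocol V9.2 to the current version is housekeeping that can be done at the same time.
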